## **2.5 Rationale and objective**

Modern regimens of CRT can lead to significant long-term survival. However the majority of patients will die of their disease, most commonly with local progression/recurrence of their tumours. Cetuximab may overcome one of the principal mechanisms of tumour radio-resistance, namely repopulation, in patients treated with CRT. There are single arm CRT plus anti-EGFR agent Phase I/II trials currently underway in patients with oesophageal cancer but there are currently no published trials of chemoradiotherapy with cetuximab in oesophageal cancer (Medline, Cancerlit), and no registered ongoing randomised trials (International Cancer Research Portfolio, PDQ). Cetuximab now has a license for treatment of patients with metastatic colorectal cancer and patients with head and neck cancer in combination with radiotherapy, therefore it is timely to assess in this disease setting.

The purpose of this research is first to determine whether the addition of cetuximab to definitive chemo-radiation (CRT) shows evidence of enhanced overall survival, shows that it is safe, and that treatment of patients with non-metastatic carcinoma of the oesophagus is feasible. If cetuximab is found to be active, safe and feasible then the trial will continue recruitment to accrue sufficient patients to establish whether the addition of cetuximab to the standard treatment improves overall survival.

### **3. PARTICIPATING CENTRE SELECTION**

This study will be carried out at participating centres within the UK who will be required to complete a site assessment form to confirm that they have adequate resources and experience to conduct the trial. As a minimum, centres must have access to and experience with EUS and multi-slice CT scans for staging and partake in appropriate specialist Upper GI MDTs which must include a specialist Upper GI surgeon. Oncologists should have appropriate experience with concurrent CRT in Upper GI Cancer.

The following documentation must be received by the Wales Cancer Trials Unit (WCTU) in order for a centre to become an approved SCOPE 1 centre.

- Confirmation of Trust R&D approval.
- Signed partnership agreement between Trust R&D department and Velindre NHS Trust.
- A copy of the most recent version of the Patient Information Sheet and Consent Form on local headed paper.
- Written confirmation that the Principal Investigator (PI) will ensure that patients and carers are appropriately competent to administer the drug capecitabine.
- Confirmation from the MHRA that centres/investigators have been added to the SCOPE 1 Clinical Trial Authorisation (CTA).
- Completed Investigator statement (signed by the PI at the centre).
- Completed delegation log (signature list and delegation of responsibilities).
- Full contact details for all site personnel.
- Set of lab normal ranges from laboratory being used for analyses.
- Pass of QA test for radiotherapy planning and treatment delivery.
- Choice of 5-Fluorouracil PVI (5FU). It is strongly encouraged that all centres use oral capecitabine but in centres who do not have access to capecitabine, treatment with 5FU is acceptable if stated before randomisation and used for all patients in both arms of the trial.

Site initiation will be by attendance at regional set-up meetings and or by teleconference or site visits. Recruitment may then commence.

Once all of the documentation has been received, confirmation of centre approval will be sent by WCTU to the Principal Investigator and the Clinical Supplies department at Merck KGaA who are supplying the cetuximab.

All this documentation must be stored in the Investigator Site File (TMF) at the centre and the Trial Site File at the WCTU. The WCTU must be notified of any changes to the trial personnel and their responsibilities during the running of the trial and the respective trial files must contain this up to date information.

## **4. TRIAL ENTRY**

### **4.1 Patient Entry**

Eligible patients will have been diagnosed with carcinoma of the oesophagus, AC, SCC, or undifferentiated carcinoma, or Siewert Type 1 or 2 tumour of the gastro-oesophageal junction (GOJ) and selected for treatment with definitive chemo-radiation by an appropriate specialised MDT. Patients are eligible for the trial if all of the following inclusion criteria (section 4.1.1) are met and none of the exclusion criteria (section 4.1.2) apply.

Any queries about whether a patient is eligible to enter the trial should be addressed to the WCTU before randomisation. Concerns will then be discussed with the Chief Investigator.

Randomisation will be performed centrally by the WCTU (Section 4.3) using a 1:1 allocation ratio. The WCTU will then send a positive entry status to confirm that the patient has been entered into the trial.

#### **4.1.1 Inclusion criteria**

Patients meeting the following criteria may be included in the trial:

1. 18 years of age or older.
2. Have been selected to receive potentially curative definitive chemo-radiation by a specialist Upper GI MDT including a designated Upper GI surgeon.
3. Not suitable for surgery either for medical reasons or through patient choice.
4. Histologically confirmed carcinoma of the oesophagus (adenocarcinoma or squamous cell or undifferentiated carcinoma) or Siewert Type 1 tumour of the gastro-oesophageal junction (GOJ) or Siewert Type 2 with no more than 2 cm mucosal extension into the stomach.
5. Tumours staged with both endoscopic ultrasound (EUS) and spiral CT scan to be T1-4, N0-1 confirming localised, non-metastatic disease (both within 7 weeks prior to randomisation, but the most recent within 4 weeks). An attempted but failed or contra-indicated EUS is acceptable. Tumours should be staged according to the 6th edition of the American Joint Committee on Cancer's (AJCC) Cancer Staging Manual (a comparative summary between the 6th and the more current 7th edition is provided in Appendix XIV).
6. Total disease length (primary and lymph nodes) less than 10cm defined by EUS (or CT if EUS attempted but failed or contra-indicated).
7. WHO performance status 0-1 (Appendix I).
8. Adequate cardiovascular function for safe delivery of chemo-radiation in the opinion of the principal investigator.
  - Where there is clinical concern patients should have an adequate cardiac ejection fraction  $\geq 40\%$  as determined by MUGA scan or ECHO (within 4 weeks prior to randomisation).
9. Adequate respiratory function for safe delivery of chemo-radiation in the opinion of the Principal Investigator.
  - Where there is clinical concern  $FEV_1 \geq 1$  litre as determined by spirometry (within 4 weeks prior to randomisation).

10. Adequate bone marrow and hepatic function (within 1 week prior to randomisation)
  - Absolute neutrophil count (ANC)  $\geq 1.5 \times 10^9/L$
  - White blood cell count  $\geq 3 \times 10^9/L$
  - Platelets  $\geq 100 \times 10^9/L$
  - Haemoglobin (Hb)  $\geq 10g/dL$  (patients' Hb should be corrected to  $>10g/dl$  before treatment)
  - Adequate liver function (within 1 week prior to randomisation)
  - Serum bilirubin  $\leq 1.5 \times ULN$
  - ALT / AST  $\leq 2.5 \times ULN$
  - ALP  $\leq 3 \times ULN$
11. Adequate renal function (within 1 week prior to randomisation)
  - Glomerular filtration rate (GFR) assessed by EDTA clearance to be  $> 40mL/min$  (or estimated by Cockcroft-Gault formula to be  $> 60 mL/min$ ) (Appendix II) (please note dose reduction for GFR 40 to 50ml/min, see p43).
12. Patients who are fit to receive all protocol treatment.
13. Patients who are able and willing to administer capecitabine.
14. Patients who are of child bearing age are willing to use contraception.
15. Patients who have completed baseline quality of life questionnaires (Appendices III and IV).
16. Patients who have provided written informed consent prior to randomisation.

#### **4.1.2 Exclusion criteria**

If any of the following criteria apply, patients cannot be included in the trial:

1. Patients who have had previous treatment for invasive oesophageal carcinoma or gastro-oesophageal junction carcinoma (not including PDT or laser therapy for high grade dysplasia/carcinoma in-situ).
2. Patients with metastatic disease i.e. M1a or M1b according to UICC TNM version 6.
3. Patients with any previous treatment for malignancy which will compromise ability to deliver definitive mediastinal chemo-radiation or may compromise survival (does not include patients with squamous cell carcinoma).
4. Patients who have had a previous malignancy during the previous 5 years.
5. Patients with significant ( $>2cm$ ) extension of tumour into the stomach.
6. Patients with unstable angina or uncontrolled hypertension or cardiac failure or other clinically significant cardiac disease.
7. Patients who have had major surgery or major trauma in the 4 weeks prior to randomisation.
8. Patients who have been treated with a monoclonal antibody in the 4 weeks prior to randomisation.
9. Patients who have been treated with radiotherapy in the 3 months prior to randomisation.
10. Patients who need continued treatment with a contraindicated concomitant medication or therapy (Refer to section 6.3).
11. Patients with known dihydropyrimidine dehydrogenase (DPD) deficiency.
12. Patients with hearing impairment or sensory-motor neuropathy of WHO grade  $> 2$  (see appendix III).
13. Women who are pregnant.

## 4.2 Pre-treatment procedures

Before randomisation, the following study procedures should be completed:

Patients must have histologically confirmed carcinoma of the oesophagus (adenocarcinoma or squamous cell) or Siewert Type 1 tumour of the gastro-oesophageal junction (GOJ) or Siewert Type 2 with no more than 2 cm mucosal extension into the stomach. This will have been determined by endoscopic assessment with biopsy.

Within 8 weeks prior to randomisation:

1. Spiral/multislice CT scan (+/- PET) (Appendix IV).
2. Endoscopic ultrasound to include recording of proximal and distal extent of primary tumour, location of lymphadenopathy and reference point for localisation on CT planning (Appendix IV).

Note: Both of these staging assessments must have been carried out within 8 weeks prior to randomisation. One of these assessments should be carried out within 4 weeks. .

Within 1 week prior to randomisation:

1. History and physical examination (to include height, weight and WHO performance status).
2. Quality of life questionnaire (QLQ-C30) (Appendix V) + oesophageal module (QLQ-OES18) (Appendix VI) and Dermatology life quality index (DLQI)(Appendix VII).
3. Full blood count.
4. Serum renal, liver and bone profile (including serum magnesium).
5. Glomerular filtration rate - calculated creatinine clearance - Cockcroft & Gault formula (EDTA/24 hour urine collection if predicted GFR <60mls/min) (Appendix II)
6. Electrocardiogram.
7. Pregnancy test in females of child bearing age.

PET scans and bone scans may be performed according to local practice and availability and/or if clinically indicated e.g. bone pain or biochemical profile. Where these scans have been performed data will be collected in the Case Report Form (CRFs).

More detailed information on how investigations such as the endoscopic assessment, biopsy, CT scan and endoscopic ultrasound should be performed are given in Appendix IV. These are recommendations and should not replace local guidelines.

Before any study related procedures are undertaken the patient's written informed consent must be obtained. The patient should be given a minimum of 24 hours after the initial invitation to participate before being asked to sign the consent form.

### 4.3 Randomisation

Randomisation will be performed centrally by the WCTU. Patients will be randomised using the method of minimisation with an element of randomisation. Minimisation will ensure balanced treatment allocation by centre and a number of potential prognostic factors. Randomisation will use a 1:1 allocation ratio.

Randomisation can only be performed after the WCTU has confirmed that the patient is eligible, the patient has signed the consent form and completed a baseline Quality of Life (QoL) questionnaire. After baseline evaluation the Research Nurse or Doctor should complete the randomisation form and telephone the WCTU:

**Randomisation Line:**  
**Wales Cancer Trials Unit**  
**[contact]**  
(Open Monday - Friday, 9am - 5pm)

At randomisation, the patient will be allocated to a treatment arm (chemo-radiation or chemo-radiation and cetuximab) and given a unique patient trial number. These details should be recorded on the randomisation form and the top copy returned to the WCTU. Randomisation details will be confirmed by fax by the WCTU. CRFs and QoL questionnaires will be sent to the Clinician, Data Manager or Nurse nominated as responsible for the patient.

It may be possible for patients to be enrolled in other clinical trials, but this will need to be discussed with the Chief Investigator or Co-Investigator.

## **5. ASSESSMENTS**

A follow up schedule is given in the following tables.

### **5.1 Baseline (pre-treatment)**

Before any study related procedures are undertaken the patient's written informed consent must be obtained. The patient should be given a minimum of 24 hours after the initial invitation to participate before being asked to sign the consent form.

**In addition to the Pre-treatment procedures (4.2) the following are to be carried out prior to treatment. The nurse/doctor will ensure the required data is recorded on the CRFs.**

1. State of Health (EQ-5D) (Appendix VIII).
2. Healthcare Resource Utilisation Log.
3. Blood sample separated and stored or posted fresh (T-SCOPE, translational research, Section 16) (Appendix IX).
4. Dysphagia scale (Appendix X).

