### 1.2 Abstract and summary of trial design

SCOPE 1 is a two arm, open, randomised Phase II/III trial. Eligible patients will have histologically confirmed carcinoma of the oesophagus (squamous cell, adenocarcinoma, or undifferentiated carcinoma) and have been chosen to receive definitive chemoradiotherapy (CRT) by an accredited multidisciplinary team (MDT) including a specialist Upper GI surgeon. 420 patients will be randomised to receive definitive CRT with or without cetuximab using a 1:1 ratio (210 patients per arm).

During the first stage (Stage 1) of the study, the trial will assess toxicity (unexpected and expected), activity and feasibility in 90 patients in the experimental arm. Activity will be measured as treatment failure-free rate and feasibility as the number of protocol dose modifications and delays. If toxicity, activity and feasibility are found to be unacceptable recruitment into the trial will stop. If the experimental arm is found to be active, safe and feasible, by the Independent Data Monitoring Committee (IDMC), recruitment will continue into the second stage (Stage 2) of the study. Stage 2 of the study will recruit a further 120 patients into each arm (a total of 420 patients) and compare the overall survival of both groups. The experimental arm of chemo-radiation and cetuximab will be compared against the control arm of chemo-radiation alone. This second stage of the trial is powered to detect a survival advantage with the addition of cetuximab.

All patients randomised into Stage 1 will contribute to the Stage 2 comparison of overall survival. In addition to overall survival, Stage 2 of the study will also assess toxicity, quality of life (QoL) and health economics.

Detailed radiotherapy treatment protocols have been notably absent in recent UK Upper GI Cancer trials involving chemo-radiation, as have procedures to assess adherence to

treatment recommendations. Therefore a detailed radiotherapy protocol and quality assurance procedure will be incorporated in this trial.

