## 6. TREATMENT REGIMEN AND SCHEDULES

### 6.1 Study treatments

Patients will be randomised to receive treatment on either of the following treatment arms.

Patients should start treatment within two weeks after randomisation.

Both arms will be delivered over 12 weeks.

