#### **Quality adjusted life years (QALYs)**

QALYs will be derived from survival data generated during the second stage of the trial and from the EQ-5D# (Appendix VIII) scores collected at baseline, during treatment and at follow-up. The patient diary will also be used to collect additional data.

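### The baseline EQ-5D is due only before treatment, not before randomisation, so in this open trial a compliant site may record the QALY baseline after allocation is known

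*Protocol*

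**What the plan says.** Section 4.2 of the protocol opens with "Before randomisation, the following study procedures should be completed". Its list for the week before randomisation includes "Quality of life questionnaire (QLQ-C30) (Appendix V) + oesophageal module (QLQ-OES18) (Appendix VI) and Dermatology life quality index (DLQI)(Appendix VII"). EQ-5D, the Healthcare Resource Utilisation Log and the dysphagia scale are not on it.

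Section 5.1 names those three items, together with a translational blood sample, as additions to the 4.2 procedures. Its timing rule is different: "the following are to be carried out prior to treatment".

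Section 4.3 allows randomisation once eligibility is confirmed and "the patient has signed the consent form and completed a baseline Quality of Life (QoL) questionnaire". Section 6.1 adds "Patients should start treatment within two weeks after randomisation", and section 1.2 states that "SCOPE 1 is a two arm, open, randomised Phase II/III trial".

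Section 15 derives QALYs from survival and from EQ-5D "scores collected at baseline, during treatment and at follow-up". Section 12.2 lists health economics as a secondary outcome of Stage 2.

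**The concern.** The protocol protects the quality-of-life baseline from knowledge of the allocation. It does not give the utility baseline the same protection, and it offers no reason for the difference. Anxiety/depression is one of the five EQ-5D items, so hope or disappointment at a known allocation could move the score in opposite directions in the two arms. A baseline recorded after allocation is no longer a pre-randomisation measurement. There is only one EQ-5D assessment before treatment and the next is at week 7, so no second baseline could replace it. Once the form has been completed late, analysis cannot undo the problem.

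**Working it through.** **Does any part of the protocol require EQ-5D before randomisation?**

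| Place | What it fixes | Does it bind EQ-5D? |
|---|---|---|
| 4.2 | Pre-randomisation list | No; EQ-5D is not listed |
| 4.3, check before randomisation | Eligibility, consent, a baseline QoL questionnaire | No; EQ-5D is not named |
| 4.3, order of steps | "After baseline evaluation the Research Nurse or Doctor should complete the randomisation form and telephone the WCTU" | Suggestive; the baseline evaluation is not itemised |
| 4.1.1, criterion 15 | Baseline quality-of-life questionnaires, with a reference to Appendices III and IV | No; EQ-5D is Appendix VIII |
| 5.5, schedule | EQ-5D is in the Screening column, whose week label is pre-treatment | Suggestive; the column also holds the translational blood sample, which Appendix IX times as pre-treatment |
| 14, timing of data collection | Baseline questionnaires before randomisation | No; the instruments of section 14 are QLQ-C30, OES18 and DLQI |
| Synopsis | Health-economics questionnaires at baseline | No timing relative to randomisation |

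No passage closes the gap. The interval the text leaves open is the one in section 6.1: nominally 0 to 14 days after randomisation.

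**Size without baseline adjustment.** The protocol states no figure to reproduce. Assume that QALYs are a trapezoid area under the utility curve, that the week 7 assessment falls about 7 weeks after baseline, and that knowing the allocation shifts the difference in mean baseline utility by d. The baseline value then has weight 0.5 × 7/52 = 0.0673 years.

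- d = 0.02: 0.0673 × 0.02 = 0.0013 QALY.
- d = 0.05: 0.0673 × 0.05 = 0.0034 QALY.

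With an interval of 6 to 8 weeks the weight is 0.0577 to 0.0769, and the range widens only to 0.0012 to 0.0038. The values of d are assumptions; the documents give none.

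**Yardstick.** Section 12.3 plans for 2-year survival of 35% against 47.5%. Under exponential survival the 2-year restricted mean is (1 − S)/λ with λ = −ln(S)/2:

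- Control: 0.65/0.525 = 1.238 years.
- Research: 0.525/0.372 = 1.410 years.
- Difference: 0.172 years. At an assumed utility of 0.7 this is about 0.12 QALY.

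The unadjusted effect is therefore 0.0013/0.12 to 0.0034/0.12, about 1% to 3% of the planned gain.

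**Size if QALYs were adjusted for baseline.** With an assumed slope of 0.3 to 0.5 of later utility on baseline utility, carried over about 1.3 life-years, the shift is d × slope × 1.3. That runs from 0.02 × 0.3 × 1.3 = 0.008 to 0.05 × 0.5 × 1.3 = 0.033 QALY. It acts in the opposite direction to the unadjusted shift, and I have ignored that small offset.

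**The case against.** The strongest reply is that the protocol uses pre-treatment as its name for the pre-randomisation phase. Section 4.2 carries that word in its heading yet opens with a pre-randomisation rule. Section 5.1 is headed as baseline and adds to that same list. Section 4.3 has the randomisation form completed after baseline evaluation. The schedule puts EQ-5D in the same column as items that must precede randomisation, and has no column between randomisation and week 1. Most of this stands: many sites would probably collect EQ-5D early. It does not make early collection a requirement, because the one sentence that sets the deadline sets it at treatment.

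A second reply is that the dysphagia scale and the resource log add little. This is right. The dysphagia scale is not among the outcome measures in section 12.2, and dysphagia as a quality-of-life aim is measured by the OES18, which is protected. The log records healthcare contacts and medication, and no route to a biased baseline is evident. Moving them is a matter of consistency.

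A reader might also infer that the QALY comparison is at risk of serious distortion, since 0.008 to 0.033 QALY is about 6% to 27% of the 0.12 QALY yardstick. The documents do not support that reading. Section 15 states no baseline adjustment, and the shift and slope are both assumed. The shift is also an arm-level mean, so it shrinks with every patient who completes the form before randomisation.

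**Conclusion.** The point holds as a loose timing rule. The text permits the EQ-5D baseline to be recorded after allocation is known, for nominally up to 14 days, in an open trial. It does not instruct sites to do so, and it would be wrong to read it as placing the utility baseline after randomisation.

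Only a secondary outcome is exposed. Overall survival, the Stage 1 endpoint and the QLQ-C30, OES18 and DLQI baselines are unaffected. The effect on the QALY difference is about 0.001 to 0.003 under an assumed shift of 0.02 to 0.05 without baseline adjustment, and larger only if an adjustment is used. The case for changing it is that the exposure is avoidable at almost no cost and cannot be repaired afterwards.

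**What to change.** - Move EQ-5D from section 5.1 into the list in section 4.2 for the week before randomisation. Move the resource log and the dysphagia scale with it for consistency.
- In section 4.3, name EQ-5D beside the quality-of-life questionnaire in the check made before randomisation.
- Record the EQ-5D completion date, so that any form completed after randomisation can be identified and examined in a sensitivity analysis.

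EQ-5D should not become an eligibility criterion, and late forms should not be discarded automatically. Discarding them would create missing baselines in order to remove an error that is probably small.

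The cost is a wording change in sections 4.2, 4.3 and 5.1, and one short form at the visit where patients already complete the other baseline questionnaires. No sample size or power figure changes.
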